## Abstract

**Introduction:**

S100B protein is a biomarker associated with central nervous system (CNS) injury following hypoxic-ischemic events. Measurement of S100B levels in umbilical cord blood may provide a noninvasive means of identifying newborns exposed to perinatal hypoxia related to fetal growth restriction (FGR) immediately after birth. Early detection of infants at increased risk of hypoxia-related CNS injury could facilitate closer surveillance, prompt diagnostic evaluation, and timely implementation of appropriate interventions, potentially improving long-term neurodevelopmental outcomes.

**Methods and Analysis:**

This study investigates two groups of full-term pregnancies: a study group with prenatally diagnosed late FGR, and a control group with normal fetal growth. Following delivery, cord blood samples from both groups will be analyzed for S100B protein concentrations, pH, base excess (BE), and lactate levels. Additionally, fetal blood flow parameters in the umbilical artery (UA), uterine arteries (UtA), ductus venosus (DV), and middle cerebral artery (MCA) will be assessed via ultrasound within 48 hours before delivery. This study aims to compare S100B protein concentrations in umbilical cord blood between the two groups and evaluate its correlations with fetal Doppler parameters, pH, BE, and lactate levels in cord blood gas analysis. Additionally, it will evaluate the potential utility of S100B protein concentration as a biomarker associated with perinatal hypoxic stress in FGR-affected neonates.

**Ethics and Dissemination:**

The study received approval from the Bioethics Committee of the Institute of Mother and Child in Warsaw (Decision No. 13/2024, dated 21 March 2024). The findings will be submitted for publication in peer-reviewed journals specializing in neonatology, pediatrics, obstetrics, and perinatology. Additionally, abstracts will be submitted to relevant national and international conferences.

**Trial registration:**

The study is registered at ClinicalTrials.gov (Identifier: NCT06893926).

## Introduction

Fetal hypoxia-ischemia (HI) presents a major challenge in perinatology due to its potential for causing severe complications in the child. Hypoxemia can result in brain damage, which may lead to conditions such as cerebral palsy, epilepsy, delayed psychomotor development, intellectual disability, and cognitive impairment [1–3].

Currently, the diagnosis of neonatal HI relies on a combination of prenatal and postnatal data. Abnormal UA and MCA blood flow parameters detected prenatally may indicate a risk of fetal HI. Postnatally, the diagnosis is based on neurological examination, laboratory tests, neurophysiological assessments, and imaging studies (such as ultrasound and MRI), along with ultrasonographic evaluation of blood flow parameters in the MCA and anterior cerebral artery (ACA) [1,3]. Despite these methods, some infants with CNS damage may not show immediate symptoms or abnormalities in additional tests after birth, highlighting the need for improved early identification strategies. Cord blood biomarkers, such as the S100B, are therefore of significant interest [1–11].

S100B is a calcium-binding regulatory protein found in the cytoplasm of brain cells. In cases of CNS damage, such as hypoxia, S100B is released into the bloodstream, resulting in elevated levels in cerebrospinal fluid and umbilical cord blood [2,8,12]. This allows for the noninvasive assessment of the biomarker’s concentration immediately after birth. Due to its short half-life, S100B facilitates the recognition and monitoring of CNS damage progression, with its concentration correlating with the severity of hypoxia. Other factors that can elevate S100B levels in a newborn’s bloodstream and cord blood include chorioamnionitis, preterm birth, prolonged vaginal labor (lasting over 15 hours), and operative delivery [5,13–17]. Conversely, significantly lower S100B levels have been observed in infants born to mothers treated with selective serotonin reuptake inhibitors (SSRIs) [18].

Higher concentrations of S100B protein have been reported in cases of chronic hypoxia, particularly in newborns diagnosed with FGR or small for gestational age (SGA), where birth weight is below the 10th percentile. However, these findings are sometimes contradictory [1–3,6]. Among neonates with FGR, significantly higher S100B concentrations have been observed in the umbilical vessels of those with abnormal prenatal blood flow in the UA compared to those with normal flow parameters [2,6]. In the FGR group, elevated S100B protein levels have also been linked to an increased risk of necrotizing enterocolitis (NEC), the need for intubation, mortality, and, according to some studies, the occurrence of intraventricular hemorrhage (IVH) [5,6]. In growth-restricted neonates, there is a noted correlation between neurological developmental disorders and blood flow parameters in the fetal MCA. However, the impact of the severity of blood flow impairment in the fetal brain on S100B concentration has not yet been studied [19].

Assessing cord blood S100B protein concentration may enable the early identification of newborns at high risk for abnormal development, even when standard biochemical or clinical parameters and neurological assessments reveal no abnormalities.

Furthermore, identifying a child at risk on the first day of life through noninvasive methods could enable early planning for systematic pediatric and physiotherapy care. This proactive approach would allow for the timely initiation of rehabilitation, potentially improving neurodevelopmental outcomes in infants affected by intrauterine growth disorders.

## Methods and analysis

The protocol was prepared with consideration of STROBE recommendations applicable to observational cohort studies [20,21] and registered at ClinicalTrials.gov (NCT06893926) on March 25, 2025 (https://clinicaltrials.gov/study/NCT06893926).

### Objectives

The study aims to:

Determine whether the cord blood S100B protein concentration is significantly higher in neonates with prenatally diagnosed FGR compared to controls.Evaluate the correlation between S100B protein concentration and fetal blood flow parameters in the UA, UtA, DV, and MCA, as assessed by ultrasound performed within 48 hours before delivery.Evaluate the discriminatory performance of S100B concentration in relation to perinatal markers associated with fetal hypoxia (pH, BE, and lactate levels in umbilical artery blood).

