#### Control Group – Exclusion criteria.

Antenatal (at recruitment):Maternal conditions that may affect placental blood flow, such as smoking, use of illicit stimulant substances, pregestational diabetes, or chronic hypertension.Maternal depression requiring pharmacological treatment (e.g., SSRIs).Risk factors for intrauterine HI, including abnormal fetal blood flow parameters on ultrasound, abnormal CTG recordings, or the need for intrauterine transfusion (IUT).Intrapartum:Indicators of possible intrauterine infection, such as amniotic fluid leakage for more than 15 hours, spontaneous preterm delivery, diagnosed intrauterine infection, or maternal symptoms of infection.Risk factors for perinatal HI.Prolonged labor lasting more than 15 hours (counted from the onset of regular uterine contractions).Birth weight below the 10th percentile or above the 90th percentile.Apgar score less than 8 at the 1st, 3rd, 5th, or 10th minute of life.Abnormal umbilical cord blood gas analysis results, defined as pH < 7.15 or BE < −9.3 mmol/l.Postnatal:Neonatal anemia requiring a top-up transfusion within the first 24 hours of life.

The exclusion criteria for the study and control groups differ based on the principle that the control group should consist of healthy neonates without risk factors for HI. In contrast, the study group includes infants diagnosed with FGR, who inherently have a higher risk of complications. These complications, such as a low Apgar score, abnormal umbilical cord blood gas analysis parameters, or an abnormal CTG recording, are precisely the factors that serve as exclusion criteria for the control group. This approach ensures that the control group provides a valid baseline for comparison against the at-risk study group.

In patients with a singleton, full-term pregnancy who present to the labor and delivery unit and meet the inclusion criteria, without meeting the antenatal exclusion criteria (except for those related to FGR), informed written consent for testing is obtained prior to delivery. The mother is also informed that if any exclusion criteria are identified during or after delivery, the child will be disqualified from further participation in the study.

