### Outcome measures

The study’s primary endpoint will be the concentration of S100B protein measured from a cord blood sample taken after birth in both the study and control groups.

Additional endpoints will include:

The potential correlation between S100B concentration and pH, BE, and lactate levels, as determined in the cord blood gas analysis in both the study and control groups.The possible relationship between cord blood S100B protein concentration and blood flow parameters (PI) in the UA, UtA, DV, and MCA, as assessed by fetal ultrasound performed within 48 hours before delivery.

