### Statistical methods

Descriptive statistics, including percentages for categorical variables and mean values, standard deviations, medians, and interquartile ranges for continuous variables, will be used to summarize the data. The Kolmogorov-Smirnov test, along with graphical analysis, will be employed to assess whether continuous variables conform to a normal distribution.

For analyzing the relationship between a quantitative variable and a qualitative variable (e.g., comparing S100B levels between the study and control groups), the Student’s t-test for independent samples will be used if the continuous variable is normally distributed. If the continuous variable does not meet the assumptions of normality, the Mann-Whitney U test will be applied instead.

To test hypotheses about the relationships between two continuous variables (e.g., S100B protein concentration versus flow rates), while accounting for confounding factors such as pregnancy duration and mode of delivery, either multivariate quantile regression or multivariate linear regression will be employed, depending on the distribution of the outcome variable.

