## Study strengths, limitations and future directions

To address the knowledge gap, the study aims to answer the following questions:Is cord blood S100B protein concentration significantly higher in infants with prenatally diagnosed late FGR, a condition associated with increased risk of hypoxic CNS injury?Does the concentration of S100B protein in umbilical cord blood correlate with blood flow parameters in the UA, UtA, DV, and MCA, as assessed by ultrasound within 48 hours before delivery?Is there an association between S100B protein concentration and pH, BE, and lactate levels in cord blood, in the context of evaluating perinatal hypoxic stress?The study procedures are straightforward and confined to a specific time point, which facilitates the accurate implementation of the study protocol.The study evaluates only short-term outcomes and does not account for the long-term neurological development of the children.In cases of urgent indications for delivery or an advanced stage of labor at admission, performing a reliable Doppler flow assessment may not be feasible.In some instances, collecting the necessary volume of cord blood for testing may be difficult due to technical problems.Due to numerous exclusion criteria in both the control and study groups, which may arise after informed consent is obtained, some patients may be disqualified during the study.

The present study may serve as a starting point for further investigations into the usefulness of S100B protein as a biomarker associated with the risk of hypoxia-related CNS injury in neonates with late FGR. Future research should consider extending the diagnostic approach to include long-term neurological follow-up, as well as additional assessment of cerebral blood flow using postnatal ultrasonography and monitoring of cerebral bioelectrical activity with amplitude-integrated electroencephalography (aEEG). Such an approach could enable evaluation of the relationship between perinatal S100B protein concentrations and subsequent neurodevelopmental outcomes in children with FGR.

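### Objective 3 promises discrimination, while the endpoint and study question specify correlation or association; the control exclusions would distort any analysis pooled over both groups

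*Protocol article*

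**What the plan says.** Objectives, third item: "Evaluate the discriminatory performance of S100B concentration in relation to perinatal markers associated with fetal hypoxia", the markers being pH, BE and lactate measured in umbilical artery blood.

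The same aim appears elsewhere in other terms:
- Abstract, Methods and Analysis: the study will "evaluate its correlations with fetal Doppler parameters, pH, BE, and lactate levels in cord blood gas analysis".
- Outcome measures, additional endpoints: "The potential correlation between S100B concentration and pH, BE, and lactate levels, as determined in the cord blood gas analysis", in both groups.
- Study strengths, limitations and future directions, third question: "Is there an association between S100B protein concentration and pH, BE, and lactate levels in cord blood".

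Statistical methods gives two tools. For a quantitative against a qualitative variable it is the t-test, with this fallback: "If the continuous variable does not meet the assumptions of normality, the Mann-Whitney U test will be applied instead". For two continuous variables, with adjustment for confounders, "either multivariate quantile regression or multivariate linear regression will be employed, depending on the distribution of the outcome variable".

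The only blood-gas cut-offs in the article are in the control-group exclusion criteria. "Abnormal umbilical cord blood gas analysis results" is defined there as pH < 7.15 or BE < −9.3 mmol/l. The accompanying text explains that such infants remain eligible in the FGR group. Lactate is not an exclusion criterion in either group.

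**The concern.** Correlation asks how S100B moves with a continuous marker. Discrimination asks how well S100B separates infants with a defined condition from those without it, which requires a reference state and a measure such as an AUC or sensitivity and specificity. An objective of the second kind with an endpoint of the first kind leaves open what the study will claim, and the choice could be made after the data are seen.

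The asymmetric exclusions make that choice consequential. At the article's own cut-offs, controls contribute no cases, so every case is an FGR infant, while controls make up about half or more of the non-cases. An AUC from such a pooled set partly measures FGR against selected healthy infants, yet could be read as performance against hypoxia. A pooled correlation has the same weakness: the groups are expected to differ in S100B and are made to differ in blood gas by selection, so part of the correlation arises between groups.

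**Working it through.** **Inputs from the article (Sample size).** Two-sided 0.05, power 80%, equal groups, about 55 per group before the allowance for non-evaluable samples. The target difference is half of 1.15, i.e. 0.575. No SD is stated, and no sample size is given for Objective 3.

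**Step 1: the implied group shift.** Because the SD is missing, the stated 55 cannot be reproduced independently; it can only be inverted.
- Normal approximation: d = (1.960 + 0.842) × √(2/55) = 0.534, so SD = 0.575/0.534 = 1.08.
- Noncentral t: d = 0.539, so SD = 0.575/0.539 = 1.07.

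The standardised shift of about 0.54 is therefore derived, not quoted.

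**Step 2: pooled AUC when S100B is unrelated to acidosis within FGR.** Let k be the acidotic FGR infants (cases). Non-cases are 55 − k FGR infants and 55 controls. Against FGR non-cases the AUC is 0.5. Against controls it is Φ(0.539/√2) = 0.648.

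Pooled AUC = [(55 − k) × 0.5 + 55 × 0.648] / [(55 − k) + 55]

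- k = 3: (26.0 + 35.7)/107 = 0.576
- k = 6: (24.5 + 35.7)/104 = 0.579
- k = 11: (22.0 + 35.7)/99 = 0.582

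So it is about 0.58 where the within-FGR value is 0.50. For shifts of 0.3 to 0.8 SD the same formula gives 0.54 to 0.62.

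**Step 3: precision of an AUC within FGR.** The article gives no acidosis rate, so 5–20% of about 55 infants (3 to 11 cases) is an assumption. The Hanley–McNeil variance with A = 0.75, Q1 = A/(2 − A) = 0.600 and Q2 = 2A²/(1 + A) = 0.643 is

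Var = [A(1 − A) + (k − 1)(Q1 − A²) + (m − 1)(Q2 − A²)] / (k·m), with m = 55 − k.

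Worked for k = 3, m = 52: (0.1875 + 2 × 0.0375 + 51 × 0.0804)/156 = 4.361/156, so SE = 0.167.

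| Cases / non-cases | SE | 95% half-width |
|---|---|---|
| 3 / 52 | 0.167 | 0.33 |
| 6 / 49 | 0.120 | 0.24 |
| 8 / 47 | 0.105 | 0.21 |
| 11 / 44 | 0.091 | 0.18 |
| 16 / 39 (about 30%) | 0.078 | 0.15 |

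**Step 4: power within FGR.** With 54 evaluable FGR infants (60 × 0.9), approximate power to separate an AUC of 0.70 from 0.50 is 21%, 31% and 53% at 5%, 10% and 20% acidotic. For an AUC of 0.80 it is 40%, 60% and 90%.

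**Step 5: what pooling would gain.** Adding 54 controls as non-cases narrows the half-width by only 0.003 to 0.010 (AUC 0.70 or 0.80, 5–30% acidotic), so it adds the distortion of Step 2 for almost no precision.

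**The case against.** A reader might infer that the design cannot deliver discrimination at all. The documents do not support that. FGR infants are not excluded on blood gas, so an AUC within that group is estimable, and a strong one would be detectable if acidosis were common (Step 4). Nor are all acidotic controls removed: the rule acts only at pH < 7.15 or BE < −9.3 mmol/l, milder acidosis remains, and lactate is not an exclusion criterion.

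It can also be said that no section plans a pooled ROC curve or a cut-off, that correlation in both groups may mean separately in each, and that a journal article may leave the ROC method and its confidence interval to a fuller document. The Mann–Whitney test is named for quantitative-by-qualitative comparisons, and U/(n1·n2) is the empirical AUC. The closing limitations paragraph describes the study chiefly as one of associations, and the asymmetric exclusions are openly justified as giving a healthy baseline for the group comparison.

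Much of this stands. The pooled bias is conditional on someone pooling, and 0.08 is smaller than the half-widths in Step 3. What does not fall away is the conflict itself: an unseen document could supply the details of a discrimination analysis, but it would not make the stated objective and the stated endpoint the same estimand.

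**Conclusion.** The point holds as a mismatch between Objective 3 and the abstract, endpoint and study question, with a specific hazard if the two groups are pooled. The mismatch rests on the text alone. The sizes rest on assumptions: the 0.54 SD shift is back-solved from 55 per group and a difference of 0.575, and the 5–20% acidosis share is assumed. Under them, a pooled AUC of about 0.58 would arise without any within-FGR association, and a within-FGR AUC of 0.75 would carry a 95% half-width of roughly 0.33 to 0.18. The primary endpoint and the sample size for the group comparison are not affected.

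**What to change.** - Reword Objective 3 as the association of S100B with continuous pH, BE and lactate, to agree with the outcome measures and the third study question.
- Estimate that association within the FGR group, or separately by group, and not pooled without regard to group. Rewording alone is not enough, because the control exclusions also distort a pooled correlation.
- If an AUC is reported, restrict it to the FGR group, define cases by the pH and BE limits already in the article, give the 95% CI, label it exploratory and derive no cut-off from it.

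No extra patients or samples are needed. The cost is a more modest claim and, if the change counts as a significant modification of the study's purpose, a formal amendment reported to the Bioethics Committee under Ethics and dissemination. It should be settled before the data are analysed.

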### Trial design

This single-center, prospective cohort study aims to assess the effectiveness of S100B protein concentration as a potential biomarker associated with perinatal hypoxic stress in neonates with FGR, compared to a control group without growth disorders.

### Study setting

The study is being conducted at the Institute of Mother and Child in Warsaw, specifically within the Department of Obstetrics and Gynecology and the Department of Neonatology and Neonatal Intensive Care, both of which function as tertiary referral units. The center manages approximately 50 full-term newborns diagnosed with FGR annually. Recruitment commenced in June 2024 and was initially projected to continue for approximately 18 months, through December 2025, with the actual duration dependent on the number of FGR patients enrolled during that period. Complete data collection is expected to be finalized within three months of the end of recruitment (March 2026), with initial results anticipated in June 2026. At the time of protocol publication, the authors anticipated potential minor delays in patient recruitment due to a lower-than-expected incidence of pregnancies complicated by FGR at the study center, as well as a higher-than-anticipated number of exclusions. As of September 2025, approximately two-thirds of the targeted patient population have been enrolled in both the study and control groups.

### Definitions

Fenton’s growth charts are used to assess birth weight percentiles [22]. The criteria for diagnosing FGR follow the 2020 recommendations of the Polish Society of Gynecologists and Obstetricians for late-onset growth restriction, which occurs after the 32nd week of pregnancy [23]. These guidelines are based on the Delphi Criteria for diagnosing early and late FGR [24].

Late FGR is diagnosed if any of the following criteria are detected during routine fetal ultrasound:

Abdominal circumference (AC) below the 3rd percentile for the given gestational age.Estimated fetal weight (EFW) below the 3rd percentile for the given gestational age.

OR

EFW or AC below the 10th percentile, along with at least one of the following:Growth retardation by the 50th percentile on the growth curve.Cerebroplacental index (CPR), defined as the ratio of the pulsatility indices (PI) in the MCA and UA, below the 5th percentile for the given gestational age.UA PI above the 95th percentile for the given gestational age.

### Eligibility criteria

#### Study group – Inclusion criteria.

Women with a full-term, singleton pregnancy (≥37 + 0/7 weeks of gestation).Pregnancy complicated by late-onset FGR.

#### Study group – Exclusion criteria.

Antenatal (at recruitment):Maternal conditions that may affect the blood flow in placental vessels, including smoking, use of illicit stimulant substances, or pregestational diabetes.Maternal depression requiring pharmacological treatment (e.g., SSRIs).Intrapartum:Factors indicating a possible intrauterine infection, such as amniotic fluid leakage for more than 15 hours, spontaneous preterm labor, diagnosed intrauterine infection, or maternal symptoms of infection.Prolonged labor lasting more than 15 hours.

Given the data on increased S100B level in labor exceeding 15 hours, this duration of amniotic fluid leakage was set as the cutoff point in the exclusion criteria [5,17].

#### Control Group – Inclusion criteria.

Women with a full-term, singleton pregnancy (≥37 + 0/7 weeks of gestation).Pregnancy not complicated by FGR.

